#### Dental startle UCS

This study will use a novel dental startle UCS previously described by Seligman et al. [23]. This stimulus is a 60 psi air puff that is delivered to a maxillary anterior tooth for 100ms through an individualized dental mouthpiece. The mouthpiece will be fabricated in visit 1 using 3 M™ STD Vinyl Polysiloxane Express Putty. The constructed mouthpiece will be used during the experimental task for all study sessions. The puff of air will be delivered to the mouthpiece with a 3/16 inch wide tubing that will receive pressurized air from a California Air Tools 8010 Steel Tank Air Compressor through an AIRSTIM device (San Diego Instruments, San Diego, California, USA). Participants will be told that the mouthpiece will allow them to experience the diverse sensations that humans can have on the alien planet.

### Measures

#### Mediating variables

We will assess *expected relevance* after the onset of the CS^+^ _P_, CS^+^ _NP_, or CS^-^ but before the onset of the startle UCS. The measure will appear in the virtual reality environment and the program will pause as participants rate the probability of a negative event occurring on a 10-point scale. Participants will use the handheld controllers to make their ratings.

To assess attention, we will track eye movements using software embedded in the Vive Pro headset. The amount of visual attention directed at the CS^+^ _P_, CS^+^ _NP_, and CS^-^ will be recorded [30, 31].

#### Subjective indicator of fear learning

The experiment will include indicators of subjective, physiological, and behavioral fear learning. In terms of subjective fear learning, participants will provide ratings of their relaxation/anxiety after the onset of the CS^+^ _P_, CS^+^ _NP_, or CS^−^ but prior to the onset of the dental startle UCS. The measure will be displayed in the virtual reality environment and participants will use the handheld controllers to make ratings [23].

#### Behavioral indicators of fear learning

We will include two indicators of behavioral fear learning. First, we will record the number of times the participant approached the CS^+^ _P_, CS^+^ _NP_, and CS^−^ and successfully obtained the “fuel cell” that appeared with alien. Second, we will measure the shortest distance between the participant and the CS^+^ _P_, CS^+^ _NP_, and CS^−^ on each trial [23].

#### Physiological indicator of fear learning

Finally, to provide a physiological index of fear learning, we will record skin conductance responses (SCRs) to the CS^+^ _P_, CS^+^ _NP_, and CS^−^. The Biopac systems MP160 with a wireless BioNomadix module transmitter (Biopac Systems, California, USA.) will be used for this assessment. SCRs will be captured with two Ag–AgCl electrodermal conductance electrodes with Isotonic gel placed on the middle phalanges of the non-dominant hand pinky and ring fingers. SCRs will be analyzed based on our prior work [32].

#### Moderator variables: pain sensitivity

We will assess *pain sensitivity* through self-report and a behavioral task. Self-reported pain sensitivity will be obtained with the Fear of Pain Questionnaire III [33] in individuals 18 years of age or older and with the Fear of Pain Questionnaire, Child report, in individuals from 6 to 17 years old [34]. Participants will complete the cold pressor test to provide a behavioral indicator of pain sensitivity [35].

### Data analysis plan

Hypotheses 1a, 2a, and 3 will be examined using SPSS software, as detailed below. Mplus software [36] will be used to address the remaining hypotheses. Note that throughout the analyses, an interaction between the two between-subjects factors is not of primary interest [19]. Rather, we anticipate that a particular combination of the groups, or the focal group, (i.e., pre-exposure with spacing and in multiple contexts) will have more favorable responses than each of the other groups. Consequently, we treat these between-subjects factors as one factor with four groups. Note that representing the four cells of the between-subjects factors in this way yields the same fit as a full between-subjects factorial model and readily enables us to assess the comparisons between the focal and other groups.

Hypothesis 1a: Spaced pre-exposure sessions, compared to no spacing, will (a) increase engagement of the proposed mechanisms (expected relevance and attention). Hypothesis 2a: Multiple context pre-exposure, as compared to pre-exposure in a single context, will (a) lead to stronger engagement of the proposed mechanisms (expected relevance and attention).

For Hypotheses 1a and 2a, changes expected in the proposed mediators should first be detected in the pre-exposure phase. To test these two hypotheses during the pre-exposure phase, a two-factor repeated measures MANOVA with one-between (pre-exposure group) and one-within-subjects (trial) factor will be run separately for the expected relevance and attention variables. A significant group × trial interaction indicates that mean responses across trials is not the same per group. If the interaction is present, follow-up analyses will focus on examining the plots of the mean change for each group and testing the degree to which the mean change from first to last trial differs between groups. For the conditioning phase, we will conduct a three-way repeated measures MANOVA separately for the two proposed mechanisms. For these models, pre-exposure groups will serve as the between-subjects factor with stimulus and trial being the within-subject factors, and the model will assess the main effects of each variable, as well as all-two-way and three-way interactions. Follow-up analyses depend on the nature of effects that are present (e.g., type of interactions or main effects). We anticipate differences will be larger between pre-exposure groups—predominantly at the early trials for stimulus CS^+^ _P_ —than for the other stimulus conditions. Thus, follow-up analyses will concentrate on the degree to which means differ by pre-exposure group and stimulus type for each trial using a Bonferonni-adjusted alpha, as well as examining plots of the mean response by stimulus type and trial for each pre-exposure group.

Hypothesis 3: Greater pain sensitivity will be associated with increased engagement of the proposed mechanisms of expected relevance and attention and increased LI.

To test the Hypothesis 3, pain sensitivity scores will be entered in the above analyses as a moderating variable. This will be done by testing interactions between pre-exposure and pain sensitivity.

Hypothesis 1b: Spaced pre-exposure sessions, compared to no spacing, will enhance LI of conditioned fear acquisition, recall, and retention. Hypothesis 2b: Pre-exposure in multiple contexts, as compared to pre-exposure in a single context, will enhance LI of conditioned fear acquisition, recall, and retention.

To investigate Hypotheses 1b and 2b, we will conduct mediation analysis to estimate direct, indirect, and total effects associated with the pre-exposure groups on the distal outcomes of conditioned fear acquisition, recall, and retention. In parallel mediation models, the pre-exposure groups are hypothesized to impact the mediators (expected relevance and attention), which, in turn, are hypothesized to affect a given fear outcome. Note that these path models do not include within-subjects variables as the scores for the mediating variables will be obtained from the first trial of the conditioning phase, where stimulus group differences are expected to be greatest, and scores from a given distal outcome will be computed as the average of the scores across specific trials in the recall and then retention phase. If the pre-exposure variable is found to interact with stimulus type in Hypotheses 1a or 2a, then this model will be estimated separately for each stimulus type to assess if mediation is present for each stimulus.

Parameters for the mediation analyses will be estimated in Mplus with maximum likelihood estimation and percentile bootstrapping (with 20,000 bootstrap samples), with the latter used to test for the presence of indirect effects. Bootstrapping is a recommended method for mediation analysis given that indirect effects are non-normally distributed [37–39], as each indirect effect is computed as a *product* of parameter estimates.

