## Methods

### Study participants

Participants will be 180 community volunteers between the age of 6 and 35, with this sample size based on an a priori power analysis for Hypotheses 1 and 2. The power analyses for Hypotheses 1a and 2a were focused on the simple pre-exposure-by-trial interaction for the conditioning and test phases. For the conditioning phase, use of G*power indicated a sample size of 19 is needed to detect a large effect, as suggested by our pilot study, (*f* = 1.3, α = 0.05, power = 0.80) whereas a sample size of 134 is needed for a given test phase to detect a small-to-moderate interaction (*f* = 0.20, α = 0.05, power = 0.80), where no prior effect size was available. For Hypotheses 1b and 2b, PASS software [24] indicated that a sample size of 106 is needed to achieve 0.80 power to detect an indirect effect equal to 0.15, where the standardized regression coefficient linking the mediator to the outcome is 0.3 and the correlation between the initiating variable and mediator is 0.5, with this correlation suggested by our pilot data.

Participants will be recruited in the regions surrounding the study sites in south Texas and northwest Ohio. It is expected that the study locations will provide the opportunity to recruit both Hispanic and African American participants, individuals that face increased burden from dental anxiety and poor oral health [11, 12]. Prior to entering the study, individuals will be screened using the inclusion/exclusion eligibility criteria displayed in Table 1. Participants will complete two or three in-person visits, depending on experimental condition, scheduled approximately 1 week apart. Participants will receive a $50 gift card for each visit. The Institutional Review Board of the primary institution approved the study.

**Table 1 Tab1:** Exclusion and inclusion criteria

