#### Task phases and manipulations

From the perspective of the participant, the virtual reality “game” will appear seamlessly in each session. However, the task consists of four distinct phases: pre-exposure, conditioning, and short- and long-term learning test phases. As described below (see Table 2), the phases occur on different days, depending on pre-exposure spacing condition.

**Table 2 Tab2:** Trials in each session as a function of experimental condition

Experimental Condition	Session 1	Session 2	Session 3
No Session Spacing/ No Context Change	-12 pre-exposure trials in Context A -36 conditioning trials -12 fear recall trials	-12 fear retention trials	-------
Sessions Spaced/ No Context Change	- 6 pre-exposure trials in Context A or Context B	- 6 pre-exposure trials in Context A or Context B -36 conditioning trials -12 fear recall trials	-12 fear retention trials
No Session Spacing/ Context Change	- 6 pre-exposure trials in Context A; - 6 pre-exposure trials in Context B -36 conditioning trials -12 fear recall trials	-12 fear retention trials	-------
Sessions Spaced/ Context Change	- 6 pre-exposure trials in Context A or Context B	- 6 pre-exposure trials in Context B or Context B -36 conditioning trials -12 fear recall trials	-12 fear retention trials

*Note* Context A refers to an environment with a brighter tan color and lighting level, whereas Context B refers to an environment with a darker green color and lower lighting level.

The first trial phase, the *pre-exposure phase*, begins with a minimum of six seconds during which the participant can traverse freely in the virtual reality environment. Participants are tasked with locating fuel canisters that are scattered across the alien planet landscape. Following the initial pre-exposure trial segment, the CS^+^ _P_ is automatically displayed, accompanied by a fuel canister, at the first opportunity. The CS^+^ _P_ are alien stimuli that have small vertical motion and customized sounds. The CS^+^ _P_ and the fuel canister will appear at a fixed distance from the participant and will stay in that location for the final six seconds of the trial. Each trial therefore contains a six second segment without the CS^+^ _P_, followed by a six second segment with the CS^+^ _P_ and fuel canister. There will be twelve pre-exposure trials and during these trials the UCS is never presented.

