The two between-subject independent variables are manipulated during the pre-exposure phase. The *pre-exposure context* independent variable has two levels: approximately half of the participants will complete the pre-exposure trials in a single context, whereas the other half will complete the pre-exposure trials in two contexts. Participants in the single context condition will complete all twelve pre-exposure trials in the same environment with a constant bright tan color and lighting level. Participants in the multiple contexts condition will complete six trials consecutively in the same bright tan color and lighting level as experienced by participants in the single context condition. The other six trials will occur consecutively with a darker green environment with a lower lighting level. Whether participants in the multiple contexts condition receive the six tan or green environment trials first will be counterbalanced. Next, the *pre-exposure session spacing* independent variable has two levels: no session spacing and session spacing. Participants in the no spacing condition will receive all twelve pre-exposure trials in their first experimental session. In contrast, participants in the spaced sessions condition will have six of the pre-exposure trials in their first experimental session, whereas the final six will occur at least 7 days later in a second session. The number of pre-exposure trials for all groups remains at twelve, to avoid confounding the number and spacing of trials. The allocation of trials across study sessions for each of the four between-subject conditions is displayed in Table 2.

Following the completion of the pre-exposure trials, participants will move to the *conditioning phase*, which will consist of 36 trials (12 CS^+^ _P_ trials, 12 CS^+^ _NP_, and 12 CS^-^ trials). The makeup of the conditioning trials will be the same as the pre-exposure trials, with the crucial difference that 75% of CS^+^ _P_ trials and 75% of CS^+^ _NP_ trials will co-occur with a dental startle UCS (explained below in the stimulus material section). The startle UCS will occur during the last 100ms of the trial and will co-terminate with the alien stimulus. The startle UCS will never be delivered on CS^-^ trials.

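### The pre-exposure follow-up compares groups on trial 12 minus trial 1 only, using one of six trials on each side of the point where the manipulations begin

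*Protocol article*

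**What the plan says.** Task phases and manipulations fixes the length of the phase: "There will be twelve pre-exposure trials and during these trials the UCS is never presented". On spacing it states: "participants in the spaced sessions condition will have six of the pre-exposure trials in their first experimental session"; the remaining trials follow no less than a week afterwards. Those in the multiple-context arms "will complete six trials consecutively in the same bright tan color and lighting level" and the other six in the darker green setting, with the order counterbalanced. Single-context participants, according to the same text, stay in tan throughout. Table 2 instead allows either context for the group with spaced sessions and a single context.

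The Data analysis plan merges the two factors: "we treat these between-subjects factors as one factor with four groups". It expects changes in the mediators to show first in pre-exposure. Expected relevance and attention are each tested there with a repeated-measures MANOVA, group by trial. If the interaction is present, the follow-up consists of plots of mean change and "testing the degree to which the mean change from first to last trial differs between groups".

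**The concern.** Both manipulations take effect between trials 6 and 7. Until then no participant has had a gap between sessions or a change of context, so each participant supplies six readings before the manipulation and six after it. The one follow-up test named for pre-exposure uses a single reading from each side and leaves ten of the twelve trials to the plots.

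Hypotheses 1a and 2a are the first link of the proposed mechanism. The plan wants to show that a particular group differs from each of the others, and the follow-up is where that would be shown. If it is noisy, a real effect of spacing or context on expected relevance or attention may look like no difference, and may be read as evidence against the mechanism.

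**Working it through.** **The plan's own figure.** The sample-size section gives 134 for a test-phase interaction (f = 0.20, alpha 0.05, power 0.80). For a repeated-measures MANOVA interaction (Pillai) with k = 4 groups and m = 4 trials, s = min(k-1, m-1) = 3, df1 = 3 × 3 = 9, df2 = 3 × (134 - 4 - 3 + 3) = 390 and noncentrality 134 × 3 × 0.04 = 16.08. Power is 0.803, so 134 is reproduced. The article's power figures for Hypotheses 1a and 2a cover the conditioning and test phases; none is given for pre-exposure.

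**Inputs.** Total 180, hence 180/4 = 45 per group (equal allocation assumed); 12 trials, split 6 + 6. The document gives no between-trial correlation, so a range is used, with trial SD 1.

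**Variances under equal correlation r**, with block-mean variance vb = (1 + 5r)/6:
- first-to-last: 2(1 - r)
- trial 12 minus mean(1-6): 1 + vb - 2r
- trial 12 adjusted for mean(1-6): 1 - r²/vb
- mean(7-12) minus mean(1-6): 2(vb - r)
- mean(7-12) adjusted for mean(1-6): vb - r²/vb

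At r = 0.5, vb = 3.5/6 = 0.583, which gives 1.00, 0.583, 1 - 0.25/0.583 = 0.571, 0.167 and 0.583 - 0.429 = 0.155. The AR(1) rows apply the same contrasts to correlations that decay with distance between trials.

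| Correlation | First-to-last | T12 change | T12 adjusted | Block change | Block adjusted |
|---|---|---|---|---|---|
| Equal 0.3 | 1.400 | 0.817 | 0.784 | 0.233 | 0.201 |
| Equal 0.5 | 1.000 | 0.583 | 0.571 | 0.167 | 0.155 |
| Equal 0.7 | 0.600 | 0.350 | 0.347 | 0.100 | 0.097 |
| AR(1) 0.5 | 1.999 | 1.380 | 1.000 | 0.674 | 0.383 |
| AR(1) 0.7 | 1.960 | 1.448 | 0.994 | 0.790 | 0.513 |
| AR(1) 0.8 | 1.828 | 1.358 | 0.962 | 0.755 | 0.546 |
| AR(1) 0.9 | 1.372 | 0.994 | 0.791 | 0.550 | 0.458 |

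Dividing the first column by the others, the gain is 1.7-2.0 times for adjusted trial 12, 1.35-1.7 for trial 12 as a change, 2.4-6.0 for block change and 3.0-7.0 for adjusted block.

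**Detectable difference**, 45 vs 45, 80% power, r = 0.5: 2.802 × √(2v/45) = 0.59 SD (first-to-last), 0.45 (trial 12, either form), 0.24 (block change) and 0.23 (block adjusted).

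**Simulated power** (2,000 runs, 45 per group, r = 0.5, constant shift in trials 7-12 of the spaced, multiple-context group, compared with the unspaced single-context group):

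| Shift | Omnibus | First-to-last | Block change |
|---|---|---|---|
| 0.2 SD | 0.23 | 0.14 | 0.64 |
| 0.3 SD | 0.53 | 0.30 | 0.93 |
| 0.4 SD | 0.86 | 0.47 | 0.99 |

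**Shape of the effect** (45 vs 45, noncentrality = contrast of the shifts / √(2v/45)). If the effect fades linearly from 0.6 SD at trial 7 to nothing at trial 12, any trial-12 contrast is at chance, while block change has power 0.94 (r = 0.5). If it grows in equal steps to 0.6 SD at trial 12 (block mean 0.35), first-to-last, adjusted trial 12 and block change have power 0.81, 0.96 and 0.98 at r = 0.5. Under AR(1) 0.8 they have 0.56, 0.83 and 0.48.

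**Colour in trials 1-6.** By the text, single-context arms are all tan and about half of each multiple-context arm is green, in either block. An assumed colour effect of 0.4 SD would make the context arms differ by 0.4/2 = 0.2 SD in both blocks. A change score removes this on average. Covariate adjustment leaves 0.2 × (1 - slope). For the block, slope = r/vb = 0.857 at r = 0.5, leaving 0.03 SD; the range is 0.01-0.06 under equal correlation 0.7-0.3 and 0.07-0.17 under AR(1) 0.9-0.5.

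**The case against.** Several stronger readings are tempting, and the document does not support them.

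- A reader might infer that all groups are treated alike through trial 6, so that trials 1-6 are a clean baseline for everything. By the text that holds for spacing only. Colour order is counterbalanced within the multiple-context arms, not between them and the single-context arms, and covariate adjustment across context would carry part of any colour effect into the comparison.
- A reader might infer that the plan discards the baseline altogether. The omnibus interaction, with (4-1) × (12-1) = 33 df, uses all twelve trials and contains the before/after contrast. First-to-last change also subtracts a pre-manipulation trial. The loss lies in the follow-up.
- A reader might add the follow-up on how "means differ by pre-exposure group and stimulus type for each trial using a Bonferonni-adjusted alpha". That belongs to conditioning, after both manipulations are complete. The article does not define its family of tests, which may be left to the analysis plan. It has no bearing on this point.
- A reader might infer that the test is invalid. In simulation without an effect, the rejection rates of the planned tests were about 0.05 or below.

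The best defence of the plan is that the state at the end of pre-exposure is a sensible target when learning accumulates, and that a block mean answers another question. This stands against replacing trial 12 by the block mean alone: the block mean has no power if an early rise is cancelled by a later fall, and under AR(1) 0.8-0.9 its gain largely vanishes for a growing effect. It does not defend trial 1 as the baseline. Taking the mean of trials 1-6 keeps the same trial-12 target and lowered the variance under every correlation tried.

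It is also fair to say that a better follow-up does not raise the chance of passing the omnibus gate that precedes it.

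**Conclusion.** The point holds as a loss of precision in one follow-up comparison. Using the trials 1-6 mean as baseline for trial 12 reduces variance 1.7-2.0 times with adjustment and 1.35-1.7 times as a simple change, with the target unchanged. Block contrasts reduce it about 2.4-7 times, but they aim at the average shift over trials 7-12 and help most when the shift is sustained.

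These figures rest on assumed correlations (equal 0.3-0.7, AR(1) 0.5-0.9), equal variance over trials and 45 per group. The size of any colour effect is unknown; 0.4 SD is illustrative only. Worth changing, since the data are already planned for collection.

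**What to change.** Keep the group-by-trial omnibus test. Replace first-to-last change with these pre-specified contrasts:

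1. **Spacing comparisons within the same context condition:** trial 12, and the mean of trials 7-12, each adjusted for the participant's mean of trials 1-6 (ANCOVA).
2. **Comparisons that involve the context factor:** trial 12 minus the mean of trials 1-6, and the mean of trials 7-12 minus the mean of trials 1-6. A constant colour offset then cancels on average, provided that the order is balanced.

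Reconcile Table 2 with the text on which colour the spaced, single-context group sees, because this decides which baselines are clean. If that group may start in either colour while the unspaced single-context group is always in tan, the spacing comparison between those two also belongs under item 2.

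The cost is analysis-plan wording, with no extra data or visits. There are two contrasts instead of one, so the plan should say which one leads or how they share alpha. The block mean blurs an effect that changes direction within trials 7-12, which is why trial 12 is kept beside it.

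### The repeated-measures MANOVAs for Hypotheses 1a and 2a discard observed trials: an incomplete record drops the person from that phase's model, and spaced participants who miss session 2 lose their six recorded pre-exposure trials

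*Protocol article*

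**What the plan says.** The Data analysis plan assigns Hypotheses 1a, 2a and 3 to SPSS. For pre-exposure it names "a two-factor repeated measures MANOVA with one-between (pre-exposure group) and one-within-subjects (trial) factor", fitted once for expected relevance and once for attention. For conditioning it states "we will conduct a three-way repeated measures MANOVA separately for the two proposed mechanisms", with group between subjects and stimulus and trial within subjects. Maximum likelihood is named only for the Mplus mediation models.

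Under Task phases and manipulations, everyone has 12 pre-exposure trials and 36 conditioning trials (12 for each of three stimuli). Under Mediating variables, attention is measured by headset: "we will track eye movements using software embedded in the Vive Pro headset". Expected relevance is a rating for which the program pauses.

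Under Study participants: "Participants will complete two or three in-person visits, depending on experimental condition". Table 2 shows what this means. The unspaced arms complete pre-exposure, conditioning and recall in session 1. The spaced arms do six pre-exposure trials in session 1. Their other six, and all of conditioning, come at least 7 days later in session 2. Under Procedure, everyone is randomised at the first visit.

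**The concern.** A repeated-measures MANOVA is computed on whole response vectors, so a person with any gap in a phase contributes nothing to that phase's model for that mechanism. With 36 required values, even rare gaps add up. Gaze recording in a headset, with participants from age 6 and with glasses or contact lenses allowed below the stated correction limit, is a likely source of gaps.

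The visit schedule adds a second route. Spaced participants can be lost between the two halves of pre-exposure; unspaced participants cannot. Under MANOVA the first half is then thrown away, and only in the arms that define the spacing comparison of Hypothesis 1a.

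At stake are precision in the mechanism analyses and the use of data already collected from randomised participants. There is a smaller consequence for the mediation models. Whether they are fitted separately by stimulus depends on an interaction found in Hypotheses 1a or 2a. That decision would rest on people with all 36 trials, whereas the mediator score needs only the first conditioning trial.

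**Working it through.** **Inputs from the article.** N: "Participants will be 180 community volunteers between the age of 6 and 35". Required values per person: 12 (pre-exposure) and 36 (conditioning). Four between-subjects groups. Test-phase requirement: "a sample size of 134 is needed for a given test phase to detect a small-to-moderate interaction", with f = "0.20, α = 0.05, power = 0.80".

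**Assumed inputs.** The per-trial loss rate p and the session-2 loss d are not in the article. Equal allocation (90 spaced, 90 unspaced) is also assumed.

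**1. The plan's own figure.** Take a group × trial MANOVA with k = 4 groups and m = 4 trials (the number per stimulus in a test phase).
- s = min(k−1, m−1) = 3 and df1 = 3 × 3 = 9.
- df2 = s(N − k − (m−1) + s) = 3 × (134 − 4 − 3 + 3) = 390.
- Noncentrality = N·s·f² = 134 × 3 × 0.04 = 16.08.
- Power is 0.803 at N = 134 and 0.799 at N = 133.

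So 134 reproduces, as a requirement for a test phase with four trials. For conditioning the article states 19 (f = 1.3). The counts below are therefore not set against 134.

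**2. Complete records under independent loss:** 180 × (1 − p)^T.

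| p per trial | T = 12 (pre-exposure) | T = 36 (conditioning) |
|---|---|---|
| 0.5% | 180 × 0.942 ≈ 169 | 180 × 0.835 ≈ 150 |
| 1% | 180 × 0.886 ≈ 160 | 180 × 0.696 ≈ 125 |
| 2% | 180 × 0.785 ≈ 141 | 180 × 0.483 ≈ 87 |

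**3. The same rates with clustering.** Independence is the pessimistic case. With a beta-binomial model and an assumed intraclass correlation of 0.1, the chance of a complete record is the product over i = 0 to T−1 of (b + i)/(9 + i), with b = 9(1 − p). For T = 36 this leaves 167, 155 and 133 of 180 at p = 0.5%, 1% and 2%. Clustering reduces the loss but does not remove it.

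**4. Missed session 2, with no other loss.** The spaced arms keep 90 × (1 − d).

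| d | Pre-exposure, MANOVA (unspaced / spaced) | Recorded trials discarded per mechanism | Pre-exposure, mixed model | Conditioning, either model |
|---|---|---|---|---|
| 5% | 90 / 85.5 | 4.5 × 6 = 27 | 90 / 90 | 90 / 85.5 |
| 10% | 90 / 81 | 9 × 6 = 54 | 90 / 90 | 90 / 81 |
| 20% | 90 / 72 | 18 × 6 = 108 | 90 / 90 | 90 / 72 |

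The last column matters. Non-returners have no conditioning trials, so changing the model does not change that imbalance.

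**The case against.** Several counter-arguments stand.
- Models are run by mechanism and by phase. A missing gaze trial removes a person from one attention model, not from the expected-relevance model or the other phase.
- Missing ratings should be rare, because the task waits for them. A short tracking dropout within a six-second stimulus display need not make the whole trial missing.
- All loss rates here are assumed. Eligibility requires availability for the whole study and each visit is paid, so loss at session 2 may be low.
- The article states no listwise rule. A fuller plan could impute before the MANOVA, and that would weaken the point.
- MANOVA leaves the covariance unrestricted, whereas a mixed model for 36 measures needs an assumed structure that may be wrong.

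Three stronger readings are tempting, and the article does not support them.
- A reader might set 150, 125 or 87 against 134 and conclude that the study falls below its planned power. The 134 belongs to a test phase, and the stated conditioning requirement is 19.
- A reader might infer that selective return biases the comparison in favour of spacing, including on fear. Nothing in the article fixes a direction, and the fear outcomes are analysed in the Mplus models, not by these MANOVAs.
- A reader might blame the MANOVA for the arm difference at conditioning. That difference comes from the schedule in Table 2.

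The core remains: the method named in the article needs complete vectors and, run as written, sets aside data that were recorded.

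**Conclusion.** The point holds as a matter of efficiency and use of data, and should be addressed. Under independent loss of 0.5% to 2% per trial, the 36-trial attention model keeps about 150 down to 87 of 180 people and the 12-trial model about 169 down to 141. Losses clustered within persons would leave more. Any loss at session 2 removes that share of the spaced arms from both pre-exposure MANOVAs although half their trials exist; the unspaced arms cannot lose people this way. The complete-vector requirement follows from the stated method and the visit difference from Table 2. The sizes rest on assumed rates, equal allocation and no prior imputation. No shortfall against the planned sample size and no direction of bias is shown. At conditioning, a better model recovers partial records of people who attended but not people who never returned.

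**What to change.** Replace both MANOVAs with linear mixed models (SPSS MIXED, REML) that keep the same fixed effects: group and trial with their interaction for pre-exposure; group, stimulus and trial with all interactions for conditioning. Use every observed trial from every randomised participant, in the arm assigned. Fix the covariance structure in advance with a fallback. One choice is unstructured across the 12 pre-exposure trials, with participant and participant-by-stimulus random effects and AR(1) trial errors for conditioning. State what makes a gaze trial usable.

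The mixed model cannot supply conditioning data for spaced participants who miss session 2. So also report return rates by arm, adjust for baseline age, site and pain sensitivity to make missing-at-random more credible, and add a sensitivity analysis for loss at session 2.

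The cost is analysis-plan wording and one further analysis, in the same software, with no change for participants. The small downside is that the chosen covariance structure may be misspecified.
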